### Study design

Prospective longitudinal controlled human infection study after intradermal injection with BCG SSI in two phases: Phase A is designed to confirm microbiological recovery and determine agreement between the current gold standard of skin punch biopsy 14 days after injection with minimally invasive biopsy techniques. Phase B is designed to refine and optimise immunological assays to measure local (using optimal minimally invasive techniques), systemic (blood) and respiratory mucosal responses to intradermal BCG injection.

**
Phase A
**

Ten participants will receive a single intradermal injection to the upper arm of BCG SSI 6–24 × 10
^5^ colony forming units in line with an optimised and established existing protocol
^
15
^. The BCG SSI strain has been chosen as the UK licensed vaccine for TB. The dose (3x higher than that used in routine vaccination) has been chosen based on study findings by Minhinnick
*et al.*
^
15
^, who demonstrated good mycobacterial recovery at this concentration with no increase in participant adverse events between the doses. Participants will be followed up longitudinally with active assessment for tolerability; adverse events; and serious adverse events. We will determine BCG SSI recovery from the intradermal injection site 14 days later by classical microbiology and molecular diagnostic techniques using gold standard punch biopsy
^
15
^ as our primary outcome measure. In parallel, and after local anaesthetic injection, we will obtain paired minimally invasive samples (skin swab, skin scrape
^
18
^ and microbiopsy
^
17
^ from the same skin site at 14 days and determine agreement of BCG SSI recovery by classical microbiology and molecular diagnostic techniques with punch biopsy

Parameters for progression from Phase A to Phase B are:

1.Participants able to tolerate study procedures2.No experimental challenge related SAE or SUSAR detected3.Confirmation of BCG recovery by classical microbiology or molecular techniques from punch biopsy at day 14 in all 10 participants who received intradermal BCG challenge4.Confirmation of BCG recovery by classical microbiology or molecular techniques from any of the minimally invasive skin sample technique (swab, scrape and microbiopsy) at day 14 in ≥9 participants who received intradermal BCG challenge.

**
Phase B
**

Twenty participants will receive a single intradermal injection to the upper arm of BCG SSI 6–24 × 10
^5^ colony forming units in line with an optimised and established existing protocol and informed by concentrations administered during Phase A
^
15
^. The focus of this phase is to apply and refine standard operating procedures to assess immune responses to intradermal injection at the local (skin), systemic (blood) and respiratory mucosal (nose) compartmental levels. We will employ a refined sampling technique substituting single punch biopsy for longitudinal minimally invasive skin sample technique(s) (as informed by phase A) to measure BCG growth kinetics and local immune responses. In parallel with local immune responses, we will measure respiratory mucosal responses in the nose to determine if/how intradermal BCG injection induces changes in the target immune compartment (respiratory system).

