## Abstract

Tuberculosis (TB) caused 1.5 million deaths in 2020, making it the leading infectious killer after COVID-19. Bacille Calmette-Guerin (BCG) is the only licensed vaccine against TB but has sub-optimal efficacy against pulmonary TB and reduced effectiveness in regions close to the equator with high burden. Efforts to find novel vaccines are hampered due to the need for large-scale, prolonged, and costly clinical trials. Controlled human infection models (CHIMs) for TB may be used to accelerate vaccine development by ensuring only the most promising vaccine candidates are selected for phase 3 trials, but it is not currently possible to give participants
*Mycobacterium tuberculosis* as a challenge agent.

This study aims to replicate and refine an established BCG CHIM at the Liverpool School of Tropical Medicine. Participants will receive an intradermal injection with licensed BCG vaccine (Statens Serum Institut strain). In phase A, participants will undergo punch biopsy two weeks after administration, paired with minimally invasive methods of skin sampling (skin swab, microbiopsy, skin scrape). BCG detection by classical culture and molecular methods will be compared between these techniques and gold standard punch biopsy. Techniques meeting our pre-defined sensitivity and specificity criteria will be applied in Phase B to longitudinally assess intradermal BCG growth two, seven and fourteen days after administration. We will also measure compartmental immune responses in skin, blood and respiratory mucosa in Phase B.

This feasibility study will transfer and refine an existing and safe model of BCG controlled human infection. Longitudinal BCG quantification has the potential to increase model sensitivity to detect vaccine and therapeutic responses. If successful, we aim to transfer the model to Malawi in future studies, a setting with endemic TB disease, to accelerate development of vaccines and therapeutics relevant for underserved populations who stand to benefit the most.

**Registration:** ISRCTN:
ISRCTN94098600 and ClinicalTrials.gov:
NCT05820594

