1.   We hypothesise that we will recover the BCG SSI strain by tissue biopsy 14 days after intradermal injection by both classical microbiological and molecular diagnostic techniques.

2.   We hypothesise that quantified BCG recovery (molecular techniques) by minimally invasive skin biopsy will be at least 90% as good as gold standard punch biopsy and will offer a more acceptable method for participants in the future.

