**Nasopharyngeal and throat swab ± saliva** Nasopharyngeal and throat combined swab will be obtained during screening visits and prior to BCG challenge (using a rapid antigen test). The aim is to determine viral infection and recognise potential asymptomatic COVID-19 cases and protect the study participants and staff. IThe PCR tests will be performed in batch at study completion and will not be used to inform study procedures.

3.   
**Blood sampling** will be performed by trained, experienced staff. Blood volumes taken at each visit are based on the safety blood screening requirements and planned exploratory immunological investigations. The total clinical blood samples taken at each visit will be 50mls, which is a maximum of 350mls over the study.

4.   
**Punch biopsy** on the intradermal injection site will be performed according to routine dermatological procedures
^
20
^. Local anaesthetic injection will be required and one to two sutures to close the biopsy site. This procedure is planned to take place in both phase A (n=10 participants) and phase B (n=20 participants) and will be used as the gold standard comparator for minimally invasive skin sampling techniques. Written consent will be taken on the same day as the procedure. The procedure will be carried out by an appropriately trained doctor or nurse experienced in this procedure.

5.   
**Minimally invasive skin biopsy** on the intradermal injection site will be performed according to published procedures
^
17
^. This procedure is well tolerated by participants, does not require local anaesthetic; and does not leave a scar. Longitudinal sampling will be performed in Phase B with two microbiopsies taken at each time point (D0, D2, D7 and D14) circumferentially around the edge of the intradermal injection site taken at intervals described in
Table 1, avoiding previous biopsy sites.

6.   
**Skin scrape** on the intradermal injection site will be performed using a rhinoprobe (see nasal sampling) curette. Our group has established standardised operating procedures using this curette for nasal sampling
^
18
^. The procedure is minimally invasive and well tolerated by participants for nasal sampling. This will not be conducted in phase B.

7.   

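### Progression criterion 4 is not tied to the skin technique that Phase B uses, so the gate can be passed while that technique misses the threshold

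*Protocol article*

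**What the plan says.** Phase A: "Ten participants will receive a single intradermal injection to the upper arm of BCG SSI". All are sampled at day 14 by punch biopsy, swab, scrape and microbiopsy. Phase B: "Twenty participants will receive a single intradermal injection to the upper arm of BCG SSI".

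Of the four progression parameters under Study design, the third requires recovery from the punch biopsy in all 10 participants. The fourth requires recovery, by culture or molecular methods, "from any of the minimally invasive skin sample technique (swab, scrape and microbiopsy) at day 14 in ≥9 participants who received intradermal BCG challenge".

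On which technique Phase B then uses, the article gives two accounts.

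- **Chosen from Phase A results.** The abstract says "Techniques meeting our pre-defined sensitivity and specificity criteria will be applied in Phase B". The Table 2 legend and the Phase B paragraph of Study design also say the technique or techniques will be selected on, or informed by, Phase A.
- **Already chosen.** Under Description of study interventions and study procedures, item 5 states "Longitudinal sampling will be performed in Phase B with two microbiopsies taken at each time point (D0, D2, D7 and D14"; item 6 says of the skin scrape "This will not be conducted in phase B"; item 7 limits the Phase B swab to ulcerated sites where secondary infection is a concern. Table 2 marks microbiopsy for Phase B at days 0, 2 and 7 and the scrape for Phase A only. Table 7 lists microbiopsy but no scrape for Phase B.

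Two further inconsistencies bear on this. Table 1 defines the longitudinal BCG endpoint by swab, and Tables 2 and 7 show the swab at every visit from day 0, contrary to item 7. Item 4 and Tables 2 and 7 keep a day-14 punch biopsy in Phase B, while the Phase B paragraph says serial minimally invasive sampling replaces it.

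**The concern.** A progression gate should test the method that the next phase depends on. This one can be opened by a method that the procedures section has removed from Phase B, and no rule covers the case where microbiopsy does badly but another technique meets the count.

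At stake is the part of Phase B that measures BCG growth over time. Items 5 to 7 leave microbiopsy as the only routine minimally invasive sample at days 2 and 7: two per visit in 20 people, so 2 × 2 × 20 = 80 samples at those visits. If microbiopsy recovers BCG in few people, low counts at those visits cannot be told apart from failed sampling, although the gate was formally passed.

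**Working it through.** The plan gives no error rate or power for the gate, so there is no figure of its own to reproduce. The check has two parts.

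**1. Does the wording allow the mismatch?** This is counting and needs no assumption.

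- If one technique must reach nine: scrape 9/10, microbiopsy 0/10, swab 0/10 meets criterion 4. Phase B as set out in items 5 and 6 then uses microbiopsy and no scrape.
- If a participant counts when any technique is positive (the pooled reading): swab, scrape and microbiopsy each positive in three different people gives 3 + 3 + 3 = 9. The criterion is met with no technique above 3/10.

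The wording permits the pooled reading but does not force it. The mismatch with Phase B exists on either.

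**2. How much could it matter?** Inputs from the article: n = 10 and a threshold of 9. Assumptions, not in the article: true recovery rate s, equal for the three techniques, ranged from 0.4 to 0.8; results independent within a person.

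- Microbiopsy alone: P₁(s) = 10·s⁹·(1−s) + s¹⁰.
- Some single technique reaches nine: 1 − (1 − P₁(s))³.
- Pooled: replace s by u = 1 − (1−s)³ and compute P₁(u).

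At s = 0.5: P₁ = 11/1024 = 0.0107; some single technique 1 − 0.9893³ = 0.032; u = 0.875, so the pooled figure is 0.639. At s = 0.6: P₁ = 0.0464; some single technique 0.133; u = 0.936, pooled 0.869.

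| s | pooled | some single technique ≥9 | microbiopsy ≥9 |
|---|---|---|---|
| 0.4 | 0.33 | 0.005 | 0.002 |
| 0.5 | 0.64 | 0.03 | 0.01 |
| 0.6 | 0.87 | 0.13 | 0.05 |
| 0.7 | 0.97 | 0.38 | 0.15 |
| 0.8 | 0.997 | 0.76 | 0.38 |

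The samples come from the same lesion, so positive correlation is plausible. It lowers the pooled column; with equal rates and full correlation it falls to the last column.

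Unequal rates show that the problem does not need pooling. With microbiopsy at 0.5, scrape at 0.9 and swab at 0.3 (again assumed and independent), the single-technique probabilities of reaching nine are 0.0107, 0.7361 and 0.0001. The chance that at least one does is 1 − 0.9893 × 0.2639 × 0.9999 = 0.739, against 0.011 for microbiopsy.

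**Specificity.** Everyone is challenged, and criterion 3 requires all 10 punch biopsies to be positive. Any Phase A that progresses therefore has no reference-negative day-14 sample, so the specificity in the abstract's selection rule cannot be estimated from it.

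**The case against.** The case on the other side is substantial, and several stronger readings do not survive it.

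- **That Phase B is irrevocably fixed to microbiopsy.** A reader of items 5 to 7 might infer this. The abstract, the Table 2 legend and the Phase B paragraph say otherwise, and Tables 1, 2 and 7 keep the swab. The accurate statement is that the article contradicts itself.
- **That 0.64 and 0.87 are the size of the problem.** They need both pooling and independence. The singular noun in the criterion and the abstract's wording fit a per-technique reading at least as well, and then the figures at 50% and 60% are 0.03 and 0.13.
- **That the skin-immune results would be uninterpretable.** Table 1 defines that endpoint by cell differentiation and antigen stimulation. Nothing makes it depend on BCG recovery, and the blood and nasal endpoints are untouched.
- **That day 14 is lost as well.** If the Phase B punch is done, day 14 keeps its gold standard and microbiopsy gets a second comparison in 20 people. Whether it is done is itself contradicted.
- **That the gate fails to test the hypothesis that recovery "by minimally invasive skin biopsy will be at least 90% as good as gold standard punch biopsy".** The article never says criterion 4 tests it. Table 1 has pairwise comparisons for that, and the estimation detail can sit in the analysis plan.
- **That the day-0 swabs could supply specificity.** No passage places them before the injection.
- **That local anaesthetic biases the gate.** Phase A states "In parallel, and after local anaesthetic injection, we will obtain paired minimally invasive samples", while the Table 2 legend and item 5 say microbiopsy needs none. The legend links anaesthetic to blunted immune responses in assays, not to lower BCG recovery, so this is only an inconsistency to reconcile.

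It is also fair that this is a feasibility study that disclaims a power basis, and that the full protocol may define the sensitivity criteria. Neither point removes the conflict, because the article states the progression parameters and the Phase B sampling itself.

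**Conclusion.** The concern holds in a limited form. Criterion 4 can be met by a technique that the procedures section does not carry into Phase B or, if positives are pooled, with no technique at 9/10. That conclusion rests on the text alone. The consequence is confined to BCG quantification: the day 2 and day 7 kinetics could rest on a technique that missed the criterion, and day 14 is protected only if the disputed Phase B punch goes ahead.

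The probabilities are illustrations under assumed equal rates and independence. At 50% or 60% recovery, the chance of passing is 0.64 or 0.87 with pooling, 0.03 or 0.13 if one technique must reach nine, and 0.01 or 0.05 for microbiopsy alone. The reading that Phase B as a whole would be invalid is not supported. This should be fixed, ideally before Phase A starts; the article reports that recruitment had not begun at submission. It does not undermine the study.

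**What to change.** 1. State criterion 4 per technique: any technique used in Phase B to quantify BCG must itself be positive at day 14 in at least 9 of the 10 Phase A participants.
2. State what follows for the BCG-kinetics objective if microbiopsy does not meet this. Microbiopsy may still be kept for the skin-immune endpoint, which needs tissue.
3. Reconcile the abstract, the Table 2 legend, the Phase B paragraph, procedure items 4 to 7 and Tables 1, 2 and 7 on which skin techniques, including the swab and the punch, are used in Phase B.
4. Delete specificity from the abstract's selection rule unless a reference-negative sample is defined.
5. Reconcile the Phase A statement that paired samples follow local anaesthetic with the statements that microbiopsy needs none.

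The cost is wording, with no extra samples. The real downside is a harder gate: a microbiopsy with 80% true recovery would reach 9/10 only about 38% of the time (10 × 0.8⁹ × 0.2 + 0.8¹⁰ = 0.268 + 0.107 = 0.376). That is why item 2 is needed alongside item 1.

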### Randomisation

Participants will not be randomised within this study.

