### Blinding and code breaking

Participants and researchers will not be blinded within this study.

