**Skin swabs** will be rolled across the intradermal injection site at each subsequent study visit to determine if BCG can be accurately recovered and quantified using this technique. There are conflicting reports in the literature on this technique: Blazevic
*et al.*
^
21
^ demonstrated that paired classical and qPCR microbiological quantification techniques demonstrated significant kinetic association. However, another study was unable to culture BCG by swabbing of the injection site
^
13
^. In phase B this procedure will only be conducted if the injection site has ulcerated and there is concern about secondary infection.

8.   
**Nasosorption** will be obtained because we expect BCG to stimulate the respiratory mucosa. Sample strips are similar to blotting paper and developed by Hunts Development Ltd (UK). Strips collect concentrated nasal lining fluid before the nasal wash to measure inflammatory responses induced by infection that may be associated with increased colonisation density and acquisition. Concentrated nasal fluid will be used to measure cytokine levels by multiplex bead array. Blotting paper will be held inside the nostril for up to 3 minutes until soaked. These will then be removed and placed in a microcentrifuge tube for storage.

9.   
**Nasal wash will be obtained in a subset of participants only.** This will be performed using a modified Naclerio method. This is a well-used and validated technique to collect nasal bacterial specimens with which we now have 4 years’ experience. Briefly, 5ml of saline is instilled and held for a few seconds in the nares before being allowed to drip in to a sterile Galli pot; this is usually repeated up to 20ml in total. In the event of NW loss (defined as cough/sneeze/swallow) the procedure may then be repeated to obtain an adequate specimen.

10.   
**Nasal cells** will be collected after nasal wash using a nanosampling method in which cells are obtained through minimally invasive superficial nasal scrape biopsies (rhinoprobe) and participants can be biopsied multiple times with no significant side effects. Up to 4 samples will be obtained at each nasal sampling visit. If no cells are visible on the rhinoprobe following sampling, the sample can be repeated immediately.

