### Statistics and analysis

**
Statistical analysis plan
**

This is a feasibility study, designed to safely transfer procedures from an established BCG controlled human infection model in Oxford to Liverpool. Experience from our collaborators in Oxford suggests that this sample size is a feasible number to recruit, screen, enrol, and follow up in practical terms, whilst also allowing the determination of any substantial differences in BCG quantification and anti-mycobacterial immunity. The sample size has not been determined with the aim of necessarily achieving statistical significance between these outcomes but to provide pilot data for future interventional trials if feasibility is confirmed.

**
Statistical methods
**

R statistical software Version 4.3.1 will be used for statistical analysis. Grouped immunological data will be assumed to be non-parametric and summarised by medians and inter-quartile ranges. Between-group comparisons will be made using the Mann-Whitney U test. The Wilcoxon Matched Pairs test will be used to make paired comparisons over time within groups. Pearson’s test of correlation will be used to analyse associations between the primary endpoint and secondary immunological outcomes.

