### Expenses and benefits

It is not intended that financial factors influence an individual's decision to participate in this study. The fees will reflect remuneration and not financial coercion. We compensate participants for time, travel, inconvenience and discomfort. The sums offered in this study have been developed over the course of many years for pneumonococcal controlled human infection studies and are consistent with remuneration in other similar local and national studies and are detailed below (
Table 7). 

**Table 7. T7:** Payment summary. The screen and vaccination appointment can be performed as a separate visit or combined as required, the remuneration will be unchanged. Participants will be provided remuneration by direct bank transfer following attendance at visit 7. Remuneration is pro-rata based on the number of visits attended and samples taken. If a participant withdraws from the study early, they will be remunerated for the visits they attended and samples which were taken up until the time they withdrew. If additional visits are required, the participant will be reimbursed for that visit.

Phase A								
	Visit 1	Visit 2	Visit 3	Visit 4	Visit 5	Visit 6	Visit 7	
Samples taken	Screening	Day 0	Day 2	Day 7	Day 14	Day 21	Day 28	
Urine	X	X						
BCG Challenge		X						
Skin punch biopsy					X			
Skin micro biopsy					X			
Skin scrape					X			
Skin swab		X	X	X	X	X	X	
Bloods	X	X	X	X	X	X	X	
Nasosorption								
Nasal cells								
Nose and throat swab	X	X	X	X	X	X	X	
Time taken	60	60	20	20	90	20	20	TOTAL
Remuneration	£40	£50	£20	£20	£150	£20	£20	£320
Phase B								
	Visit 1	Visit 2	Visit 3	Visit 4	Visit 5	Visit 6	Visit 7	
Samples taken	Screening	Day 0	Day 2	Day 7	Day 14	Day 21	Day 28	
Urine	X	X						
BCG Challenge		X						
Skin punch biopsy					X			
Skin micro biopsy		X	X	X	X			
Skin swab		X	X	X	X	X	X	
Bloods	X	X	X	X	X	X	X	
Nasosorption	X	X	X	X	X	X	X	
Nasal cells	X	X	X	X	X	X	X	
Nose and throat swab	X	X	X	X	X	X	X	
Time taken	60	60	60	60	90	60	60	TOTAL
Remuneration	£40	£55	£55	£55	£150	£55	£55	£465

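### Phase B asks whether BCG causes nasal immune changes, but its single-arm, within-person comparison cannot separate BCG from the effect of repeated nasal sampling

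*Protocol article*

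**What the plan says.** All places are in the protocol article.

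- **Aim.** Under Study design, Phase B, nasal responses are measured "to determine if/how intradermal BCG injection induces changes in the target immune compartment (respiratory system").
- **Who is challenged.** "Twenty participants will receive a single intradermal injection to the upper arm of BCG SSI" (Study design). Under Randomisation: "Participants will not be randomised within this study".
- **Nasal schedule.** Table 2 marks nasosorption, nasal wash and nasal scrape for Phase B only, on days 0, 2, 7, 14, 21 and 28. Wash is for a selected subset.
- **Sampling intensity.** For the curette scrape: "Up to 4 samples will be obtained at each nasal sampling visit" (Description of study interventions and study procedures).
- **Nasal endpoints.** Table 1 lists cell differentiation and activation, and cytokine expression.
- **Test.** "The Wilcoxon Matched Pairs test will be used to make paired comparisons over time within groups" (Statistics and analysis).
- **Viral swabs.** Table 2 schedules nasal and throat swabs at every Phase B visit, partly to look for respiratory viruses. The procedures section adds: "PCR tests will be performed in batch at study completion and will not be used to inform study procedures".
- **Sampling effects.** The Discussion names the effect of serial microbiopsy on the immune response as a possible limitation, mitigated by sampling different places around the lesion. It has no matching statement for the nose.
- **Screening.** The Phase B block of Table 7 (Expenses and benefits) also marks nasosorption and nasal cells at screening, which Table 2 does not. The Table 7 note says: "Remuneration is pro-rata based on the number of visits attended and samples taken". It also allows screening and vaccination to be combined in one visit.

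**The concern.** The word 'induces' claims cause. The planned comparison has as its null hypothesis that nothing has changed since day 0, whatever the reason. Sampling begins at the day 0 visit, when BCG is given, so every later nasal sample follows both the challenge and earlier scrapes of the same nose. With up to four scrapes at each of six visits, the day 28 sample can follow as many as 5 × 4 = 20 earlier scrapes. Scraping could plausibly move the general inflammatory readouts in Table 1. Nobody goes through this sampling without BCG, and Phase A has no nasal immune samples to serve as a reference.

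The mucosal time course is part of what the Discussion presents as not previously done. If a shift from day 0 were read as a mucosal response to BCG, the trial could pass on to later vaccine studies a signal that its design cannot attribute. The reverse can also occur: a sampling effect in the opposite direction could hide a real response.

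**Working it through.** **There is no planned figure to reproduce.** The article gives no significance level, effect size or power for the nasal comparison, and says the sample size was not set to reach statistical significance. The check concerns what the stated test responds to.

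**1. Model.** For participant i at one post-challenge visit, let

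Dᵢ = Yᵢ(visit) − Yᵢ(day 0) = β + s + vᵢ + error,

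where β is the BCG effect, s the effect of earlier nasal sampling and vᵢ the effect of any new viral infection. The signed-rank test asks whether D is centred on zero. In a single arm only the sum of β, s and vᵢ is observed, so β is not identified. This needs no numerical assumption.

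**2. Inputs for the illustration.**
- From the article: n = 20, all challenged.
- Assumed: two-sided 0.05, normal data, equal within-person correlation ρ of 0.5 to 0.7, and s of 0.25 or 0.5 SD.
- Exact Wilcoxon signed-rank at n = 20: critical value 52, true size 0.0484.
- SD of D = σ√(2(1 − ρ)), which is 1.00σ at ρ = 0.5 and 0.77σ at ρ = 0.7.

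**3. Rejection at one visit with no BCG effect** (100,000 simulations per cell):

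| Sampling shift s | ρ = 0.5 | ρ = 0.7 |
|---|---|---|
| 0 | 5% | 5% |
| 0.25 SD | 18% | 27% |
| 0.5 SD | 54% | 76% |

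**4. Equivalence of causes (ρ = 0.5).**
- β = 0.5, s = 0: 54.1%.
- β = 0, s = 0.5: 54.0%.
- β = 0.25, s = 0.25: 54.4%.
- β = 0.5, s = −0.5: 4.7%, so a real effect is masked.

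**5. Virus alone.** Here only a fraction of participants shift, by an assumed 1 to 3 SD of the paired difference:
- 10% infected: 6.5 to 10% rejection.
- 20% infected: 11 to 25%.
- 30% infected: 19 to 49%.

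This is weaker than a shift in everyone. Entry rules that exclude recent respiratory infection do mean that new infections would mostly fall after baseline.

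**6. Would subtracting the screening-to-day-0 change repair it?** Suppose screening samples exist and sampling causes a constant shift s from the second sample onward. The means are then 0 at screening, s at day 0 and s + β after challenge.
- Visit minus day 0 has mean (s + β) − s = β, which is unbiased.
- (Visit − day 0) − (day 0 − screening) has mean (s + β) − 2s + 0 = β − s, which is biased.
- Its variance is (1 + 4 + 1)σ²(1 − ρ) = 6σ²(1 − ρ), against 2σ²(1 − ρ): three times as large.

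Simulated over ρ = 0.5 to 0.7, the subtracted test rejects 22 to 34% when s = 0.5 and β = 0. It rejects 5% when s = β = 0.5, so the real effect cancels. When s = 0 and β = 0.5 its power is 22 to 34%, against 54 to 76% for the plain comparison.

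If each sampling visit instead added an equal increment, the subtraction would work at day 2, where (2s + β) − 2s = β, but not at day 7, where (3s + β) − 2s = β + s. The documents do not say which pattern applies.

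**The case against.** The strongest reply has four parts.

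- **This is a feasibility study.** The nasal response is one secondary outcome, Phase B concentrates on refining procedures, and the article says it seeks pilot data. That excuses imprecision and limits how much weight the point carries. It does not make a within-person change attributable to BCG.
- **No document shows that nasal scraping shifts these readouts.** This is true, and the percentages above are only power against an assumed shift. The article does say that repeated nasal biopsy has no significant side effects, but that concerns tolerability, not stability of cytokines or cell activation.
- **The viral swabs are already there.** The article says PCR will not inform study procedures, which leaves its use in analysis open, and an unseen analysis plan may provide for it. This stands, so the viral part is minor. An analysis plan could not, however, supply an unchallenged comparison.
- **Table 7 is a payment table.** Its screening crosses for nasal samples bring no extra time or money: screening is 60 minutes and £40 in both phases. On days 2, 7, 21 and 28, by contrast, Phase B rises from 20 minutes and £20 to 60 minutes and £55. It is weak evidence that screening samples are planned.

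A reader might go further and infer three things that the documents do not support. The first is that virus misleads the test as readily as BCG would; step 5 shows otherwise unless infection is common and its effect large. The second is an inflated error rate from counting any significant visit among five, about 19% with no shift at all; that presumes a decision rule the article never states. The third is that wash affects everyone, when it is confined to a subset.

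**Conclusion.** The point holds as a limit on inference. The stated aim is causal, while the single-arm design and within-person test support only a statement about change after challenge under repeated sampling. That conclusion follows from the article's own design and does not depend on the simulation.

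The size is illustrative: about 18 to 27% rejection at one visit for a 0.25 SD sampling shift and about 54 to 76% for 0.5 SD, with no BCG effect. It rests on assumed alpha, correlation, normality and shift size. If repeated sampling has no effect, the test keeps its nominal level.

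It would be too strong to conclude that the nasal data are uninformative, that a nasal finding would be false, or that the Wilcoxon test is the wrong test of change. The weakness is moderate and can be corrected without altering the sampling.

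**What to change.** 1. **Wording.** State the nasal aim and conclusion as change after challenge under repeated sampling. Name repeated nasal sampling as a limitation beside the one already given for microbiopsy. Reserve 'induced by BCG' for changes supported by readouts specific to BCG or mycobacterial antigen. The general cell and cytokine endpoints in Table 1 do not by themselves meet that standard.
2. **Sensitivity analysis.** Repeat the nasal analysis without visits that are positive on the viral PCR already being collected.
3. **Reconcile Table 2 with the Phase B block of Table 7** on whether nasosorption and nasal cells are taken at screening. If they are, keep day 0 as the baseline and report the screening-to-day-0 change descriptively, as an indication of a sampling effect. Note that it is unavailable where screening and challenge are combined.
4. **Do not test post-challenge change minus screening-to-day-0 change**, for the reasons in step 6 of the working.

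An unchallenged group sampled on the same schedule would separate the causes. With a 0.5 SD drift in both groups (in SDs of the change score), a Mann-Whitney test on change rejects 5.1% at 20 versus 20 when BCG has no effect. Its power for a 0.5 SD effect is only 33%, so it is not proposed for a feasibility study of this size.

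The cost is a more cautious claim and one extra analysis on existing data.
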